## Results

The 10 vignettes necessary to carry out the study were successfully created, and the maximum safe doses were determined. These vignettes and the doses were checked and approved by all authors. The 10 vignettes, as well as their English translation, were presented to peer reviewers but are not publicly available to avoid any potential bias. They will nevertheless be published along with the results paper.

The sample size calculation was performed using Stata (version 17.0). It showed that 46 participants (23 in each group) would be needed to detect a 10% difference with a power of 90%, taking into account an SD of 10%. In line with the above methods, a total of 50 anesthesiologists should therefore be recruited. Since there are 62 residents and 52 registrars in the HUG Anesthesiology Department, a participation rate of 44% (50/114) will be necessary. This participation rate seems achievable with the aforementioned recruitment procedure. If this rate cannot be achieved, other Swiss University hospitals will be contacted, and similar recruitment procedures will be carried out to obtain the required sample size.

The study platform has been successfully created and tested by all coauthors [22]. The data extraction mechanisms have also been successfully checked.

The recruitment will take place once this study protocol has been reviewed and accepted for publication to allow for any necessary adjustments before study inception. The current version of the protocol is 0.9 (October 10, 2023). The published version will be 1.0.

It should be possible to start recruitment during the winter of 2023. This would allow data analysis to take place in spring 2024, and results should be submitted for publication in an international peer-reviewed journal by the end of the same year.

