### Study Design

This will be a monocentric, parallel-group, randomized controlled trial based on clinical vignettes. The protocol was developed according to the Standard Protocol Items: Recommendations for Interventional Trials (SPIRIT) statement (Multimedia Appendix 1) [14]. Given its design, the investigators will not be blinded as to the intervention. Nevertheless, participants will not be informed that there are 2 different arms and will not be told the exact outcomes studied, even though they will be provided with general information regarding the study. In addition, the data analyst will be blinded as to participant allocation by renaming the groups before sending data for statistical analysis. Randomization will be stratified according to current position (resident vs registrar).

Results will be reported according to the CONSORT-EHEALTH (Consolidated Standards of Reporting Trials of Electronic and Mobile HEalth Applications and onLine TeleHealth) guidelines [15]. Relevant elements of the CHERRIES (Checklist for Reporting Results of Internet E-Surveys) will be included since web-based questionnaires will be used in the course of this study [16].

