### Clinical Vignettes

A total of 10 clinical vignettes will be developed for the purpose of this study. These vignettes will describe clinical cases requiring the use of LAs for regional anesthesia. We will include 3 of the most commonly used LAs in these vignettes: lidocaine, levobupivacaine, and ropivacaine. Some vignettes will ask the participant to use LA mixtures, and several will include comorbidities or medications requiring dose adaptations.

For each vignette, 3 authors will be required to determine the maximum dose of LA the simulated patient should receive according to the rules used to develop the LoAD Calc app [12], without using the app. These rules, which are derived from the scientific literature, are summarized in Textbox 1. They were reviewed and approved by clinical pharmacologists and toxicologists [12]. Any disagreement will prompt a review of the vignette. Final vignette approval will only be possible if a consensus can be reached.

Dosage elements and app rules used to calculate the maximum safe dose of local anesthetics, adapted from Suppan et al [12].

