### Inclusion and Exclusion Criteria

All resident physicians and registrars working in the HUG anesthesiology department will be eligible for inclusion. The only exclusion criteria will be current or previous use of the LoAD Calc app. This criterion will be assessed by a screening question asked after the completion of all study vignettes.

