### Recruitment

The project will first be presented to the head of the anesthesiology department and then to all consultants. After obtaining their agreement, investigators will recruit potential participants directly in the operating room. These residents and fellows in anesthesiology will be informed that the study will last at most 1 hour and that an investigator will replace them in the operating room while they participate. They will be told that participation is entirely voluntary, that there will be no consequence if they refuse to participate, and that they will be able to withdraw at any time without explanation. No incentive other than advancing scientific knowledge will be given to promote participation. They will be given a paper sheet summarizing the information regarding the study and data protection (Multimedia Appendix 2). Those who agree will be scheduled for participation on the same day. Together with the anesthesiology consultant overseeing the operating room, an investigator will organize replacements to avoid any disruption in the operating program. There will be only 1 slot, and therefore, only 1 participant per hour.

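### One fixed set of 10 vignettes passes one participant at a time through a single department, and no listed questionnaire item would reveal prior knowledge of the cases

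*Protocol article*

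**What the plan says.** The Results section states that the vignettes and their translation were "presented to peer reviewers but are not publicly available to avoid any potential bias" and will be published with the results paper.

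The other relevant statements in the protocol article are these:

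- **Clinical Vignettes:** "A total of 10 clinical vignettes will be developed for the purpose of this study". No second set and no varied order is described.
- **Inclusion and Exclusion Criteria:** "All resident physicians and registrars working in the HUG anesthesiology department will be eligible for inclusion". The exclusion is for use of the app: "The only exclusion criteria will be current or previous use of the LoAD Calc app".
- **Recruitment:** investigators approach people in the operating room. "Those who agree will be scheduled for participation on the same day", and "There will be only 1 slot, and therefore, only 1 participant per hour".
- **Results:** "a participation rate of 44% (50/114) will be necessary".
- **Study Design:** "participants will not be informed that there are 2 different arms and will not be told the exact outcomes studied".
- **First questionnaire (Consent and Study Sequence):** the itemised pages cover consent, awareness and use of LoAD Calc, and demographics. One item records whether the participant has heard of LoAD Calc. None concerns the cases.
- **After the vignettes:** the app arm completes the usability scale, the control arm names its methods, and both rate their confidence. Again nothing concerns the cases.

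Possible leakage between participants is not among the limitations in the Discussion.

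**The concern.** Withholding the vignettes from publication protects against outside readers. The people best placed to pass the cases on are earlier participants, who work in the same operating rooms as those still to be recruited. Nearly half of the eligible staff must be tested before the sample is complete.

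The answer key is built from the same rules as the app. A control who learns from a colleague which adjustments the cases call for moves towards the key. An app user gains less, because the app already applies those rules. Knowledge of the cases would therefore tend to narrow the difference in overdose rate. It could also shorten completion times in either arm, and the direction of that effect on the time comparison cannot be predicted.

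The gap matters because it cannot be repaired later. Without a question asked at the session, a small observed difference could not be separated into a small true effect and leakage.

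**Working it through.** **Step 1: the safeguards in the text, set against the route of leakage.**

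| Safeguard | Where | Does it cover talk between colleagues about the cases? |
|---|---|---|
| Vignettes unpublished until the results paper | Results | No; it covers outside readers |
| Arms and exact outcomes not disclosed | Study Design | No; it limits what investigators say, not what participants say |
| Quiet room, phones in flight mode | Consent and Study Sequence | No; it protects the session only |
| Testing on the day of agreement | Recruitment | Partly; it shortens the gap after agreeing, not earlier talk |
| Exclusion for use of LoAD Calc | Inclusion and Exclusion Criteria | No; it concerns the app |
| Item on having heard of LoAD Calc | First questionnaire | No; it concerns the app |

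No row measures prior knowledge of the cases.

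**Step 2: reproduce the plan's own figures.** Inputs from Results and Statistical Analysis: difference 10 points, SD 10 points, two-sided alpha 0.05, power 90%, equal groups. For a two-sample t-test the noncentrality is d / (SD × √(2/n)), with 2n − 2 degrees of freedom.

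- n = 22 per arm: 10 / (10 × √(2/22)) = 3.317, power 0.8997, just short of 90%.
- n = 23 per arm: 3.391, power 0.912. This gives 46 in total, as stated.
- n = 25 per arm (the target of 50): 3.536, power 0.934.
- Participation: 50/114 = 43.9%, stated as 44%.

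**Step 3: an illustration of dilution.** The documents give no disclosure rate. Assume that a share p of controls is informed and that each informed control loses the entire 10-point difference. The expected difference is then 10 × (1 − p). With 25 per arm and SD 10:

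| p (assumed) | Difference | Noncentrality | Power |
|---|---|---|---|
| 0 | 10 | 3.536 | 0.934 |
| 0.1 | 9 | 3.182 | 0.877 |
| 0.2 | 8 | 2.828 | 0.791 |
| 0.3 | 7 | 2.475 | 0.679 |

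Mixing informed and uninformed controls also widens the control-arm variance to 100 + p(1 − p) × 100. At p = 0.1 this is 109, so the average SD is √((100 + 109)/2) = 10.22 and power is 0.862. At p = 0.2 it is 116, the average SD is 10.39 and power is 0.760.

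Losing the whole difference is the extreme case for each informed control. If each lost only half, p = 0.2 would give a difference of 10 × (1 − 0.2 × 0.5) = 9, the same difference as in the 0.1 row.

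**The case against.** The strongest reply is that the article contradicts itself nowhere here and that much of the risk may already be handled. Its parts deserve separate answers.

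- **The information sheet (Multimedia Appendix 2) and the consent wording are not shown and could ask for confidentiality.** This stands. A reader might infer that nothing at all restrains disclosure; the documents do not support that, since the texts where such a request would normally sit cannot be read. What can be read is the itemised questionnaire, and it has no question on the cases.
- **Knowledge of the app is already addressed.** This largely stands. Users are excluded, and having heard of the app is recorded. The gap concerns the cases.
- **Little of value can be passed on.** This stands in part. No feedback of correct answers is described, so a control has no known-correct answers to share, and recalling volumes over 10 varied cases is hard. Remembering that a case turns on ideal weight, a comorbidity or an interacting drug is easier.
- **A positive result would not be undermined.** This stands for the overdose rate. Randomization should spread informed participants over both arms, so the expected effect is dilution.

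A reader might also infer that exclusions caused by leakage would exhaust the margin between 46 and 50. The documents do not support that as a serious threat. Five exclusions leave 45, and a 22/23 split still gives power of about 0.906 under the plan's assumptions. The rounding up was made for attrition and exclusions, and the Results section allows recruitment at other Swiss university hospitals.

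**Conclusion.** The point holds as a gap in detection. The plan accepts that advance knowledge of the vignettes is a bias, uses one fixed set sequentially among close colleagues, and lists no item that would show whether leakage occurred. The likely consequence for the primary outcome is a contrast biased towards no difference, with some loss of power; completion times may be distorted as well.

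The size is unknown. The fall from 93% to about 88% or 79% (86% or 76% with the wider control variance) rests on assumed shares of 10% and 20%, on complete loss of the difference in each informed control, and on the plan's own SD of 10 points. It shows what leakage of that extent would cost, not that it will happen. This is an inexpensive improvement to make before recruitment, not a flaw that invalidates the design.

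**What to change.** 1. **Closing screen, after the vignettes:** ask all participants not to discuss the cases or the session with colleagues until recruitment closes, unless the information sheet or consent already does so. Keep it after the vignettes and do not mention a tool. Mentioning a tool before the vignettes would hint to controls that one is under test and work against the concealment of the arms.
2. **First questionnaire, before the calculation method is displayed:** add one neutral item, identical in both arms, asking whether a colleague has told the participant about the study cases. At that point the answer cannot be coloured by having used the app.
3. **Analysis:** prespecify a sensitivity analysis of the primary outcome without those who answer yes. For knowledge of the app, use the existing item on having heard of LoAD Calc. That item is informative only if asked before the app is handed over. The study sequence places the app-use screening in the first questionnaire, whereas the Inclusion and Exclusion Criteria section places it after the vignettes; the two sections should be reconciled.

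The cost is one sentence, one question and one extra analysis. The question relies on self-report, and the sensitivity analysis will include slightly fewer participants. The design, vignettes and sample size do not change.

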## Discussion

### Overview

This study should allow us to determine whether LoAD Calc, an mHealth app designed to calculate maximum safe LA doses, is safer and more effective than current clinical practice. Previous studies have shown that mHealth apps can enhance dose calculation and potentially improve safety [23], decrease time to drug delivery [23], and lessen stress [24]. Assessing this latter parameter would not make much sense given the design of this study but could prove interesting in future high-fidelity or field trials.

Other solutions have already been proposed for the calculation of the maximum safe LA dose but present significant drawbacks. Some of them, such as the nomogram created by Williams and Walker [11], do not depend on technological devices. This nomogram, which represents a rapid and calculation-free way, must, however, always be within reach. In addition, IBW must first be determined, and there is no dose adaptation based on health conditions or drug interactions. Computer-based solutions and mobile apps have also been created, such as MDCalc Local Anesthetic Dosing Calculator [25], The Podiatry Institute’s LA Toxic Dose Calculator [26], and SafeLocal by Johns Hopkins Digital [27]. All these solutions lack key elements and do not consider either IBW, comorbidities, or medications. Most allow invalid data to be entered or suggest doses exceeding the maximum safe dose, thereby presenting potential safety issues.

No study can be devoid of limitations, and the one planned according to this protocol is no exception. The first foreseeable limitation is that the LoAD Calc app will be compared to many different methods of LA dose calculation, thereby preventing us from directly comparing this app to a specific method. However, there is no gold standard to calculate the maximum safe LA doses, and the design of the proposed study can be considered pragmatic. Another limitation is that the maximum safe doses will be calculated using the same scientifically grounded rules that were used to develop LoAD Calc [12]. However, some of the calculation rules used by the app are not supported by strong scientific evidence, and there is no gold standard for comprehensive, safe calculation of maximum LA doses. Finally, the results obtained through this study will only apply to the single-dose administration of a limited number of LAs or of LA mixtures. This will not affect the validity of the study’s results nor compromise the use of the app since the 3 LAs selected (levobupivacaine, lidocaine, and ropivacaine) are commonly used in clinical practice. Nevertheless, further app developments will be needed to take other LAs and repeated doses into account. Since some LAs, such as lidocaine, are also safe for intravenous use, future versions of the app should enable practitioners to select different injection sites and routes.

### Conclusions

Following this protocol should enable us to determine whether LoAD Calc, a mHealth app designed to calculate the maximum safe doses of LA, is both safe and effective. If this hypothesis proves to be true, clinical trials could be considered, and further outcomes, such as the impact of LoAD Calc on cognitive load and physiologic stress, could be considered.

## Appendix

Multimedia Appendix 1 SPIRIT checklist.

Multimedia Appendix 2 Study information sheet.

## Abbreviations

CCER: Commission Cantonale d’Ethique de la Recherche
CHERRIES: Checklist for Reporting Results of Internet E-Surveys
CONSORT-EHEALTH: Consolidated Standards of Reporting Trials of Electronic and Mobile HEalth Applications and onLine TeleHealth
HUG: Geneva University Hospitals
IBW: ideal body weight
LA: local anesthetic
LAST: local anesthetic systemic toxicity
LoAD Calc: Local Anesthetics Dose Calculator
mHealth: mobile health
SPIRIT: Standard Protocol Items: Recommendations for Interventional Trials
